**Methods:**

This is a pilot Hybrid Type 3 implementation trial. Four Michigan communities primarily serving the Native American families and already using *Family Spirit* were randomized by site to receive Standard Family Spirit or Precision Family Spirit. Participants include *N* = 60 mothers at least 14 years of age (pregnant or with a newborn < 2 months of age) currently enrolled in Family Spirit. Precision Family Spirit participants receive core lessons plus additional lessons based on needs identified at baseline and that emerge during the trial. Control mothers receive the standard sequence of Family Spirit lessons. Data is collected at baseline (< 2 months postpartum), and 2, 6, and 12 months postpartum. All Precision Family Spirit participants are invited to complete qualitative interviews at study midpoint and endpoint. All home visitors are invited to participate in focus groups between study midpoint and endpoint. Exploratory data analysis will assess feasibility, acceptability, client-home visitor relationship, retention, adherence, and potential differences in intervention outcomes.

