#### Primary outcomes

Our primary outcomes of interest include participant acceptability, satisfaction, quality of relationship between home visitor and client, retention, and adherence. Acceptability is measured from the perspective of the participant using a 15-item scale [16] administered at study midpoint and endpoint. Satisfaction is captured through a 34-item questionnaire used in the Family Spirit trials and adapted specifically for this study and administered at midpoint (around 6 months postpartum) and endpoint. All Precision Family Spirit participants are invited to participate in a short qualitative interview to further explore acceptability and satisfaction using an 11-item interview guide. In addition, we will explore home visitor acceptability and satisfaction through focus group discussions that follow a 9-item interview guide. The quality of the relationship between home visitor and client is captured using the short version of the Working Alliance Inventory (WAI) administered to both participant and home visitor. The WAI measures three domains of the relationship: goal alignment, task alignment, and bond. Retention is measured by comparing the number of participants who drop out in each study arm. Adherence is measured by comparing the percentage of retained participants in each study arm who completed their lessons as prescribed.

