#### Primary aim analysis

As this is a pilot study, most data analysis will be exploratory, but based on best practices in the field to analyze clinical trial data. We will conduct an “intent to treat” analysis as the primary analysis approach. Baseline demographic characteristics will be explored to examine comparability between the groups. For continuous measures, we will explore average scores and distributions at each time point. To test for effects, we will use mixed-effects regression models (MRMs) to estimate average differences between outcomes on the standard vs. precision approaches using the scores on the acceptability, participant satisfaction, and home visitor-client relationship assessments. Specifically, we will add a dichotomous indicator for participants receiving the precision approach compared to the standard approach and examine the interaction of that dichotomous indicator with the change in outcome measure. The MRMs will include random effects at the individual and site levels to account for multiple time points within an individual and clustering by site. We will also examine the differences in proportion of participants who dropped out and who received 50% dosage using mixed effects logistic regression models accounting for clustering by site. For all analyses, we will report both unadjusted and adjusted analyses (adjustment based on differences in baseline demographics between the two groups at the *p <* 0.1 level). For all qualitative data, we will use thematic analysis to analyze interview transcripts using Dedoose software [37]. As transcripts are reviewed, “memos” will be generated to document initial impressions of topics and themes. Segments of transcripts will then be assigned codes based on a priori (i.e., from the interview guide) or emergent themes (i.e., open coding) [38].

All analyses for the secondary outcomes will be done on an exploratory basis only.

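### The primary outcome adherence is defined as completion of prescribed lessons among retained mothers, but the primary aim analysis specifies no analysis of it and instead models receipt of 50% dosage among participants

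*Protocol article*

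**What the plan says.** The Primary outcomes section lists the primary outcomes as "participant acceptability, satisfaction, quality of relationship between home visitor and client, retention, and adherence". It defines the last two. For retention: "Retention is measured by comparing the number of participants who drop out in each study arm". For adherence: "Adherence is measured by comparing the percentage of retained participants in each study arm who completed their lessons as prescribed". Table 2 also places adherence among the primary objectives, and Table 1 names it as an implementation outcome that the strategy should affect.

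The Primary aim analysis section opens with the analysis population: "We will conduct an “intent to treat” analysis as the primary analysis approach". Mixed-effects regression is then planned "using the scores on the acceptability, participant satisfaction, and home visitor-client relationship assessments". The binary outcomes follow: the article will examine "differences in proportion of participants who dropped out and who received 50% dosage", by mixed effects logistic regression that allows for clustering by site. Adherence, completion of prescribed lessons and a retained-only denominator are not mentioned in that section. The 50% dosage measure appears there and nowhere else in the article.

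The abstract adds a general statement without a method: "Exploratory data analysis will assess feasibility, acceptability, client-home visitor relationship, retention, adherence, and potential differences in intervention outcomes".

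**The concern.** A reader who matches the outcomes to the analyses finds a planned model for acceptability, satisfaction, relationship quality and retention. The fifth primary outcome has none. Where its analysis would be expected, there is a different measure with a lower threshold and a wider population.

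Two things are at stake. First, the article leaves open which figure will be reported as adherence, so the choice could be made after the data are seen. Second, the defined version is a comparison within retained mothers. The strategy is meant to change retention, so the retained groups in the two arms may be different kinds of mothers. A strategy that keeps mothers who would otherwise have left can lower adherence among the retained even if no mother completes fewer lessons. The pilot is intended to supply estimates for a full trial, so an ambiguous adherence figure would carry forward into that design.

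**Working it through.** The article states no rate, power or sample size for adherence or for 50% dosage, so there is no figure to reproduce. The check is a comparison of the two sections, followed by arithmetic on what the difference can do.

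**1. The two measures side by side**

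| | Primary outcomes section | Primary aim analysis section |
|---|---|---|
| Name | Adherence | 50% dosage, not called adherence |
| Threshold | Lessons finished as prescribed, no number given | 50%, base not stated |
| Population | Retained mothers in each arm | Participants, under intent to treat |
| Method | Comparison of percentages, no model | Mixed effects logistic regression with clustering by site |

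**2. The thresholds in lessons**

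The section on Standard Family Spirit prescribes 47 lessons to 12 months postpartum. The section on Precision Family Spirit prescribes 25 to 41.

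- Half of 47 is 23.5, so 24 lessons.
- Half of 25 is 12.5, so 13 lessons. Half of 41 is 20.5, so 21 lessons.

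If 50% means a common count instead of each mother's own prescription, 24 lessons is 24/47 = 51% of the Standard programme, 24/41 = 59% of the longest Precision programme and 24/25 = 96% of the shortest. The article does not say which is meant.

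**3. Can the two measures disagree?**

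Hypothetical counts, assumed only to show the mechanism: 30 enrolled per arm (equal arms are an assumption, since allocation is by site). In Standard, 15 are retained and 9 complete. In Precision, 25 are retained and 10 complete. Every retained mother reaches 50% and no mother who leaves does.

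| Measure | Standard | Precision | Precision minus Standard |
|---|---|---|---|
| Completed, among retained (adherence as defined) | 9/15 = 60% | 10/25 = 40% | −20 points |
| Completed, among enrolled | 9/30 = 30% | 10/30 = 33% | +3 points |
| 50% dosage, among retained | 15/15 = 100% | 25/25 = 100% | 0 points |
| 50% dosage, among enrolled (as analysed) | 15/30 = 50% | 25/30 = 83% | +33 points |

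The first and last rows have opposite signs. The first two rows isolate the denominator: Precision has one more completer out of 30, yet looks 20 points worse once the comparison is limited to retained mothers.

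**4. How far apart could the thresholds be?**

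The article gives no completion rates, so this is an assumption shown over a range. Lessons completed follow a beta-binomial distribution with mean m and correlation ρ of 0.1 or 0.2, giving parameters a = m(1/ρ − 1) and b = (1 − m)(1/ρ − 1). Completion as prescribed is read as every lesson, which the article does not state.

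| Mean m | Reach 50% (25 or 47 lessons) | Complete all 25 | Complete all 47 |
|---|---|---|---|
| 0.5 | 50% | 0.1–0.8% | 0.01–0.2% |
| 0.7 | 80–88% | 2–7% | 0.4–3% |
| 0.9 | 97–99% | 28–42% | 18–34% |

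The two thresholds give clearly different percentages at each mean. Where each falls depends on the assumed mean.

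**The case against.** The strongest reply is that the article does not abandon adherence. Its definition speaks of comparing the arms, and the abstract lists adherence among what will be assessed. A reader might infer that adherence will never be analysed. The documents do not support that. They support only the narrower statement that the analysis section specifies no analysis of adherence as defined.

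A reader might also infer that 50% dosage has been substituted for adherence. The article never says so, and it may be an additional exposure measure. If it was meant as the working form of adherence, the definition under Primary outcomes is the one that does not fit. Either way the sections need reconciling.

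A third tempting reading is that both cut-points are uninformative, with full completion near the floor and 50% near the ceiling. That rests on one assumed mean and on reading completion as every lesson. At a mean of 0.5, only half of mothers reach 50%. At 0.9, full completion is 18–42%. The claim is not made here.

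Finally, this is a condensed article about a pilot whose analysis is mostly exploratory, and operational detail may sit in the full protocol. That limits the seriousness. It does not remove the mismatch, because the article states two different measures of lesson completion and does not relate them.

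**Conclusion.** The point holds as an inconsistency between two stated sections. The primary outcome adherence and the planned lesson-dose analysis differ in threshold (prescribed completion against 50%) and in population (retained mothers against participants under intent to treat). This rests on the text alone.

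The possible size is shown by the hypothetical counts: −20 points on one measure and +33 on the other for the same mothers. Those counts are assumed and do not predict this trial's results. The retained-only denominator is a weakness in its own right, because retention is another primary outcome that the strategy is intended to change. In an exploratory pilot this should be corrected, but it does not undermine the other planned comparisons.

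**What to change.** Make the Primary outcomes and Primary aim analysis sections state one adherence outcome, with one threshold and one population. To match intent to treat, analyse it in all enrolled mothers and report the completion percentage among retained mothers descriptively.

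The definition should also settle two details:
- whether 50%, if kept, refers to each mother's own prescribed lessons or to a common count;
- how the prescribed number is set for a Precision mother who leaves early, since lessons are added as needs emerge and her total would not be fully determined.

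The proportion of prescribed lessons delivered, as a continuous measure, is one option and not a requirement. It needs the same denominator rule.

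The cost is a revised definition and that rule. The article describes participant tracking throughout the study but does not say outright that each delivered lesson is recorded, so this should be confirmed. The downside is that adherence in all enrolled mothers partly reflects dropout, so it should be presented beside retention.

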## Methods/design

### Trial design

This study uses a two-arm pilot randomized Hybrid Type 3 design [14]. Four Family Spirit home visiting sites from the Inter-Tribal Council of Michigan (ITC of MI) were selected based on comparability and randomized using a 1:1 allocation to provide either Standard Family Spirit or Precision Family Spirit to their clients. Sites were matched based on annual volume of clients served and geographic similarity (i.e., urban vs. rural) (Fig. 1).

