This modularized approach to Family Spirit is called Precision Family Spirit. Precision Family Spirit was developed using mixed methods, including a secondary data analysis to identify meaningful subgroups that could inform how and when to tailor, and stakeholder workshops with program implementers (supervisors and home visitors) to identify core lessons, and lessons relevant to certain subgroups of clients [9, 16]. It consists of five lesson “pathways” that have been identified through formative work across Family Spirit’s national network of stakeholders [9]. There is a core set of lessons that every mother receives. For this pilot study, that means all Precision Family Spirit participants should receive 25 lessons from pregnancy to 12 months postpartum (the duration of enrollment). She receives additional lessons based on her emergent needs identified through data collection at home visits and at each assessment timepoint (Additional file 1). Thus, a Precision Family Spirit participant could be scheduled to receive between 25 and 41 lessons from pregnancy to 12 months postpartum. For example, if a participant is a first-time mother, she (and her family) will receive 6 additional baby care lessons (covering basic topics such as diapering and how to dress a baby) that are included in the Standard Family Spirit curriculum but may not be relevant for experienced mothers with previous children.

The study uses the Care4 implementation platform, which is a secure, HIPAA-compliant web-based application designed to capture data for the purposes of program implementation and evaluation [19]. Care4 is configured to notify home visitors when a participant needs to be added to any additional lesson pathways. Precision Family Spirit participants are assessed at each lesson visit using a measurement-based care approach [20–22] to understand and respond to emergent needs and help home visitors better track how their clients are doing over time. These short assessments are estimated to take 1–2 min to complete at each visit. Lessons are delivered in the same format as Standard Family Spirit, by trained home visitors in the home of the participant or a private place of their choosing.

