### Limitations

There are some limitations to this pilot study. First, we focused on content delivery (i.e., prescribed active ingredient) of the Family Spirit model. However, the home visitor-client relationship (e.g., unprescribed active ingredient) could be the focus of implementation strategies in home visiting [7, 39]. Results of data collected in this pilot trial through the Working Alliance Inventory will help us explore the quality of the home visitor-client alliance to understand whether tailoring content impacts this relationship.

Second, there was a small number of groups randomized into each study arm. Only four ITC of MI sites were included in this pilot trial. Therefore, we are unlikely to achieve completely comparable groups. However, within the context of these limitations, the results of this pilot trial can inform a fully powered cluster randomized trial in the future.

Third, there are some concerns regarding generalizability of study findings. Yet, a strength of this pilot study is that was designed for Native American communities, which are the most historically disenfranchised racial/ethnic subgroup in the US facing substantial behavioral health and sociodemographic disparities [40–42]. Positive findings in this population may provide promise for translation into other communities.

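### Adjustment covariates are chosen by a baseline test at p < 0.1, a criterion unrelated to whether they predict the outcome; a short fixed list would serve better

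*Protocol article*

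**What the plan says.** The Primary aim analysis section of the protocol article says that for every analysis "we will report both unadjusted and adjusted analyses", and defines the adjusted version in parentheses: "adjustment based on differences in baseline demographics between the two groups at the" p < 0.1 level. It names no covariate, gives no other selection criterion, and does not say whether the baseline test allows for site. Candidates are limited to demographics.

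The design sections matter here. Sites, not mothers, were "randomized using a 1:1 allocation" (Trial design), and "Sites were matched based on annual volume of clients served and geographic similarity". Under Limitations the authors write "Only four ITC of MI sites were included in this pilot trial" and accept that "we are unlikely to achieve completely comparable groups".

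Two baseline features have an evident link to what is delivered or observed. Under the precision strategy, "if a participant is a first-time mother, she (and her family) will receive 6 additional baby care lessons", on top of a 25-lesson core. The inclusion criteria admit women at any point from pregnancy to two months after birth, so the number of lessons still available and the time in which to drop out vary between women.

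**The concern.** A covariate is worth adjusting for when it predicts the outcome. A baseline significance test looks only at the other half of the question, whether the arms differ, and it does so with a threshold set by sample size. It can therefore go wrong in both directions: a strong predictor with a moderate imbalance is left out, and an irrelevant demographic that happens to differ is put in.

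The rule is stated outright and covers every adjusted analysis, so it is not a detail left open for an analysis plan; a plan that followed it would inherit the problem. The pilot is meant to supply estimated effects and variability for a full trial. Adjusted estimates whose covariate set depends on chance p-values, and which forgo available precision, serve that purpose less well than they could.

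**Working it through.** The p < 0.1 threshold is a rule, so there is no figure to reproduce. The stated detectable effect of d = 0.8 (Sample size calculation and statistical analysis) is used below only as a yardstick; whether it is itself correct is a separate matter.

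**Inputs from the article:** N = 60, four sites, two per arm, threshold p < 0.1. **Assumed, because the article does not give them:** 30 mothers per arm and 15 per site, the number of demographics tested, the ICC of a demographic between sites, and the correlation of a covariate with the outcome.

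**1. Imbalance that escapes the screen (test ignoring site).** Critical standardised difference = t(0.95, 58 df) × √(2/30) = 1.672 × 0.258 = 0.43 SD. For a binary trait near 50% it is 1.645 × √(0.25 × 2/30) = 21 percentage points. Chance that a true imbalance is flagged:

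| True imbalance | Flagged |
|---|---|
| 0.2 SD | 20% |
| 0.3 SD | 31% |
| 0.4 SD | 46% |
| 0.5 SD | 61% |

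**2. Chance selection.** With k independent demographics, no true imbalance and no clustering, P(at least one flagged) = 1 − 0.9^k: 41% for k = 5, 57% for k = 8, 65% for k = 10.

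**3. Four sites.** The result depends on a choice that the article does not state.
- *Test ignores site.* With design effect 1 + 14 × ICC, the flag rate is 2 × [1 − Φ(1.645/√(design effect))]. At ICC 0.01, 0.05 and 0.10 the design effects are 1.14, 1.70 and 2.40, and the flag rates are 12%, 21% and 29% instead of 10%.
- *Test respects site.* With four site means there are 2 df and t(0.95) = 2.92. The imbalance needed is 2.92 × 0.258 = 0.75 SD at ICC 0, and 2.92 × √(2/30 × 1.70) = 2.92 × 0.337 = 0.98 SD at ICC 0.05.

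So the screen either selects too much or selects almost nothing.

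**4. Largest shift from an unflagged imbalance.** Shift = imbalance × correlation. Just under the threshold, at 0.42 SD:

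| Assumed correlation | Shift | Share of d = 0.8 |
|---|---|---|
| 0.3 | 0.13 SD | 16% |
| 0.5 | 0.21 SD | 26% |
| 0.7 | 0.29 SD | 37% |

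**5. Average cost.** Simulation of one continuous covariate, 30 versus 30, no clustering, 20,000 trials per scenario:

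| Correlation | SD of estimate: unadjusted | screened at p < 0.1 | always adjusted | Type I error: screened | always adjusted |
|---|---|---|---|---|---|
| 0.5 | 0.259 | 0.246 | 0.226 | 0.041 | 0.050 |
| 0.7 | 0.259 | 0.230 | 0.186 | 0.032 | 0.051 |

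Screened against always adjusted, the SD is 0.246/0.226 = 1.09 times as large at correlation 0.5 and 0.230/0.186 = 1.24 times at 0.7. In the roughly 15% of simulated trials where the imbalance exceeded 0.3 SD but was not flagged, the unadjusted type I error was about 0.069, against 0.043 to 0.052 with fixed adjustment.

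**The case against.** The strongest reply is that little harm follows. The rule is declared beforehand and uses no outcome data, so it does not let the analyst pick a favourable result. An unadjusted analysis, which involves no selection, always stands beside the adjusted one. The trial is a pilot, described as mostly exploratory, and its authors already concede imbalance. In the simulation, screening still beats no adjustment on precision, and its type I error falls below 5%, not above it. All of this stands, and it limits the size of the point.

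Three stronger readings are tempting and are not supported:

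- *That the rule leaves important imbalance unadjusted as a matter of course.* That is a risk, not a certainty. If the test ignores site, clustering pushes the other way and more variables are flagged.
- *That results will be biased by about 0.2 SD.* That figure takes the largest imbalance that escapes the screen and multiplies it by an assumed correlation. Nothing in the article shows that any demographic correlates 0.5 with satisfaction, acceptability or alliance.
- *That restricting candidates to demographics deprives the primary outcomes of baseline adjustment.* Table 2 has no baseline for acceptability, satisfaction or the Working Alliance Inventory, and retention and adherence cannot have one. The restriction matters only for secondary outcomes, where a mixed model may already use the baseline score as a repeated measure.

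It is also fair to say that the article does not show first-time motherhood or stage at enrolment to predict the primary outcomes. They are reasonable candidates because of how lessons are assigned and when women enter; the choice remains a judgement.

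None of this justifies the selection criterion itself, which is uninformative about prognosis in any of these circumstances.

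**Conclusion.** The point holds at moderate weight. The stated rule selects adjustment covariates on a criterion unrelated to prognosis. With about 30 per arm, it passes over observed imbalances below about 0.43 SD and admits irrelevant variables by chance. With four sites it over-flags or hardly flags, depending on an unstated choice of test. The expected cost is a covariate set that depends on the data and some lost precision: an SD about 9% larger at an assumed correlation of 0.5, and about 24% larger at 0.7. The shift of about 0.2 SD is a worst case.

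These sizes rest on equal arms and sites and on assumed ICCs and correlations, and the simulation leaves out clustering. The case against the rule itself does not depend on those assumptions. A reader might infer that a fixed covariate list would make the arms comparable. It would not: with two sites per arm, differences between sites remain confounded with the arm comparison whatever individual covariates are used.

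**What to change.** - Remove the p < 0.1 screen.
- Name a short set now and use it in every adjusted primary-aim model, for example first-time mother (yes/no) and pregnant versus postpartum at enrolment. N = 60, or 42 after 30% attrition (60 × 0.7), does not support many more.
- For secondary outcomes with a baseline in Table 2 (EPDS, perceived stress, parent knowledge, quality of life, ASSIST), also account for the baseline score, either as a covariate or as a repeated measure in the mixed model, and say which.
- Describe baseline characteristics by arm and by site, without p-values.
- State that covariate adjustment does not remove site-level confounding with two sites per arm.

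The cost is a change of analysis wording. No new assessment should be needed: pregnancy or infant age is an eligibility item, first-time motherhood is one of the risk categories behind the tailoring, and the baseline scores are already scheduled. The team should confirm that first-time motherhood is recorded at the standard sites as well, since home visitors there are not notified of it.

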### Randomization

Participating ITC of MI sites were randomized to use the Precision Family Spirit implementation strategy or Standard Family Spirit (control condition). Randomization occurred before recruitment began at the site level. The four sites were selected based on comparability of annual volume of clients served and geographic similarity (i.e., urban vs. rural). Once sites were matched, the study team flipped a coin to decide which sites would be assigned to each study arm. Participants are blind to whether they receive Standard Family Spirit or Precision Family Spirit as randomization occurs at the site-level. Thus, all participants at each site receive the same version of Family Spirit (standard or precision).

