#### Quality assurance

To ensure quality of participant consent procedures, all study staff have been certified to consent participants. Home visitors received initial in-person training on informed consent. Post-training, they had to demonstrate mastery of a full informed consent procedure with their supervisor prior to being certified. Program supervisors used a checklist to certify home visitors at their site.

Quality assurance of lesson delivery for both study arms occurs according to existing ITC of MI procedures. All home visitors are required to pass knowledge tests on each lesson prior to administering them to clients. Further, they must complete role plays and achieve a total average score of at least 3 out of 4 on a quality assurance form administered by a supervisor or program manager. To ensure ongoing high quality of lesson delivery, home visit observations are conducted at least biannually and ideally quarterly. For home visitors with at least 5 years of experience implementing Family Spirit, they are observed annually or more frequently if desired by the home visitor. Home visitors participating in this pilot trial are, in general, experienced in delivering Standard Family Spirit*.* Of 13 trained home visitors, 8 (62%) have at least 5 years of experience as Family Spirit certified home visitors. Further, 11 (85%) have at least 3 years of experience. All home visitors have been trained for at least a year before this pilot trial launched.

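### Covariates for every adjusted analysis are picked by a p < 0.1 test of baseline demographics, so a prognostic imbalance can be left in and an irrelevant one adjusted for

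*Protocol article*

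**What the plan says.** Under Primary aim analysis the article states: "For all analyses, we will report both unadjusted and adjusted analyses". The parenthesis that follows defines the adjusted version: "adjustment based on differences in baseline demographics between the two groups", with the threshold set at p < 0.1. No covariate is named, only demographics are eligible, and relation to outcome is not a criterion.

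Three other places bear on this:

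- **Unit of randomisation.** Trial design says the four sites "were selected based on comparability and randomized using a 1:1 allocation", and Randomization adds: "Randomization occurred before recruitment began at the site level". So there are two sites per arm.
- **Handling of site.** Primary aim analysis puts a site random effect in the mixed models and accounts for site clustering in the logistic models for dropout and 50% dosage. It does not say how the baseline comparison treats site.
- **Expected balance.** Limitations concedes that "we are unlikely to achieve completely comparable groups".

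**The concern.** A baseline variable distorts the arm comparison only if it is both unbalanced and related to the outcome. A p-value for baseline imbalance addresses the first condition alone, and in a sample of 60 it does so with low sensitivity. A moderate imbalance in a strong predictor can therefore be passed over while a chance difference in an unrelated variable is adjusted for.

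Randomisation by site adds to this. Mothers at one site tend to resemble each other, so a test that treats them as independent will reach p < 0.1 more often than its nominal rate.

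At stake are the adjusted estimates. The article wants its estimated effects to inform a full trial, and it expects imperfectly comparable arms. Parity shows how a relevant variable can be missed. In the Precision arm, "if a participant is a first-time mother, she (and her family) will receive 6 additional baby care lessons", so parity bears on prescribed dose and hence on adherence. Under the rule it is adjusted for only if it counts as a demographic and happens to cross p < 0.1.

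**Working it through.** The article gives no figure for this rule, so there is none to reproduce.

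**Inputs from the article:** N = 60; four sites, 1:1; 30% attrition; threshold p < 0.1; detectable effect d = 0.8.

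**Assumptions (not in the article):** 30 mothers per arm and 15 per site; covariate ICC of 0 to 0.20; covariate-outcome correlation r of 0 to 0.5; 5 to 10 demographics.

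**1. Imbalance needed to enter.**

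- Continuous variable: t(0.95, 58) × √(2/30) = 1.672 × 0.258 = 0.43 SD.
- Binary variable, uncorrected chi-square: 15/30 v 21/30 gives p = 0.11 (not entered); 15/30 v 22/30 gives p = 0.063 (entered).
- Chance that a true difference is flagged: 20% at 0.2 SD, 31% at 0.3, 46% at 0.4 and 61% at 0.5.

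**2. What an unflagged imbalance can do.** The shift in the arm difference is about r × imbalance. Just under the threshold this is 0.3 × 0.43 = 0.13 SD, or 0.5 × 0.43 = 0.22 SD. These are the largest shifts that one unflagged covariate can cause at those correlations.

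**3. Chance entries with no clustering.** The probability that at least one of k independent covariates is flagged is 1 − 0.9^k: 41% for k = 5, 57% for k = 8 and 65% for k = 10.

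**4. Effect of site randomisation on a mother-level test.** From 40,000 simulated trials per setting:

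| Covariate ICC | Flagged at nominal 10% |
|---|---|
| 0 | 10% |
| 0.01 | 12% |
| 0.05 | 21% |
| 0.10 | 30% |
| 0.20 | 42% |

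A test on the four site means (2 degrees of freedom) returns to about 10% at every ICC.

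**5. Cost in precision.** From 6,000 simulated trials per setting, with one outcome measurement, least squares, no treatment effect and no site effect on the outcome beyond the covariate. Entries are root mean squared error of the arm difference in outcome SD:

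| ICC | r | Unadjusted | p < 0.1 rule | Always adjusted | Rule v always |
|---|---|---|---|---|---|
| 0 | 0.5 | 0.257 | 0.246 | 0.228 | +8% |
| 0.05 | 0.5 | 0.277 | 0.243 | 0.223 | +9% |
| 0.10 | 0.5 | 0.299 | 0.248 | 0.231 | +7% |
| 0 | 0.3 | 0.258 | 0.255 | 0.249 | +2% |
| 0.05 | 0.3 | 0.266 | 0.255 | 0.250 | +2% |
| 0.05 | 0 | 0.265 | 0.267 | 0.269 | −1% |

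In the same runs, observed imbalances above 0.25 SD went unflagged about 69% of the time at ICC 0, 53% at 0.05 and 43% to 45% at 0.10.

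**6. Room in the dropout model.** 60 × 0.30 = 18 expected dropouts. That supports very few covariates, and the rule sets no limit on how many enter.

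**The case against.** The strongest reply is that little rests on the adjusted model. The article calls most of its analysis exploratory and bases the sample size on feasibility, and every unadjusted result is reported alongside. The rule and its threshold are stated in advance and use baseline data only. A reader might infer that the covariate set could be steered by the outcome results, but the text gives no support for that. All of this stands and limits the severity.

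A reader might also infer that the adjusted analysis is the plan's only protection against confounding by site. It is not. Sites were matched on client volume and urban or rural setting before the coin flip, and site is in the outcome models. Nor could a better covariate list do that job: with four sites, no covariate adjustment removes site-level confounding.

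The precision loss depends on r, which the article does not give; the 8% figure needs a strong predictor. If sites differ, the rule also misses fewer imbalances, and at r = 0.5 it recovers about 63% (ICC 0.05) and 75% (ICC 0.10) of the gain from always adjusting. An imbalance produced by site differences is still real in the sample, so flagging it is not in itself an error. The fault is that flagging says nothing about prognosis.

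Finally, the simulation is not the planned mixed model. With complete data and a random intercept, a baseline covariate entered as a main effect leaves the arm-by-time interaction unchanged. The point therefore concerns the average arm differences, which the article also plans to estimate, and the logistic models. The linear simulation does not size the effect on the latter.

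None of these replies supplies a reason to select on a baseline p-value.

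**Conclusion.** The criticism holds, at modest severity. The rule is fixed in the text for all adjusted analyses, selects without regard to prognosis, and is silent on site in the baseline test. At about 30 per arm it admits only observed imbalances above about 0.43 SD. If the test is run at mother level, it flags irrelevant variables at about two to three times the nominal rate for ICCs of 0.05 to 0.10. The loss against always adjusting is about 8% in standard error at r = 0.5, about 2% at r = 0.3 and nil near r = 0.

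These are statements of what can happen, with probabilities. They do not show that a real imbalance will be left in or an irrelevant variable will be adjusted for. They rest on assumed equal arms and sites, ICC and r, and the simulations ignore the site matching, which could lower the flag rates for covariates that track the matching factors.

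A reader might also want home-visitor experience as a required covariate, given "Of 13 trained home visitors, 8 (62%) have at least 5 years of experience". The article does not support this: it ties experience to how often visits are observed, not to any outcome, and 13 visitors over four sites leave it entangled with site.

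**What to change.** Delete the p < 0.1 rule. Before analysis:

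- Name a short set of baseline covariates already collected, chosen on expected prognosis, for example first-time mother (yes/no), pregnant or postpartum at entry, and maternal age. The article does not list its demographic items, so confirm that each is recorded in both arms.
- Use that set in every adjusted analysis, whatever the observed imbalance.
- Limit the dropout model to one or two of these, given about 18 expected events.
- Describe baseline balance by arm and site without p-values.
- Keep the unadjusted results alongside.

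The cost is a wording change, with no new data. A few degrees of freedom are spent on covariates that may prove balanced or only weakly prognostic; in the r = 0 setting above, this moved the error from 0.267 to 0.269.
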